## 8 ADVERSE EVENTS

### 8.1 Monitoring of Adverse Events

The definitions of Adverse Events (AEs) and Serious Adverse Events (SAEs) are given below. It is of the utmost importance that all staff involved in the study be familiar with the content of this section. The Principal Investigator is responsible for ensuring this.

### 8.2 Events Definitions

An **Adverse Event (AE)** is the development of an undesirable medical condition or the deterioration of a pre-existing medical condition following or during exposure to a pharmaceutical product, whether or not considered causally related to the product. An undesirable medical condition can be symptoms (eg, nausea, chest pain), signs (eg, tachycardia, enlarged liver) or the abnormal results of an investigation (eg, laboratory findings, ECG). In clinical studies, an AE can include an undesirable medical condition occurring at any time, including run-in or washout periods, even if no study treatment has been administered.

Any detrimental change in a patient's condition subsequent to them entering the study and during the follow-up period should be considered an AE. When there is a deterioration in the condition for which the study treatment is being used, there may be uncertainty as to whether this is lack of efficacy or an AE. In such cases, unless the reporting physician considers that study treatment contributed to the deterioration or local regulations state to the contrary, the deterioration should be considered a lack of efficacy. Signs and symptoms of disease progression are therefore not considered AEs.

The development of a new cancer should be regarded as an AE. New cancers are those that are not the primary reason for administration of study treatment and have been identified after inclusion of the patient into the clinical study.

**A Serious Adverse Event (SAE)** is an AE occurring during any study phase (ie, run-in, treatment, washout, follow-up), and at any dose of the investigational product, comparator or placebo, that fulfills one or more of the following criteria:

- Results in death
- Is immediately life-threatening
- Requires inpatient hospitalization or prolongation of existing hospitalization
- Results in persistent or significant disability or incapacity
- Is a congenital abnormality or birth defect
- Is an important medical event that may jeopardize the patient or may require medical intervention to prevent one of the outcomes listed above.

Any event or hospitalization that is unequivocally due to progression of disease, as determined by the investigator, must not be reported as an SAE, however should be communicated to AstraZeneca.

The causality of SAEs (their relationship to all study treatment) will be assessed by the investigator(s) and communicated to AstraZeneca. Causality is a determination of whether there is a reasonable possibility that the drug may have caused or contributed to an adverse event. It includes assessing temporal relationships dechallenge/rechallenge information, association (or lack of association) with underlying diseases, and the presence (or absence) or a lack of one or more likely causes.

The Investigator must attempt to determine if an adverse event is in some way related to the use of the study drug. This relationship should be described as follows:

Unlikely: The event is clearly due to causes distinct from the use of the study drug, such as a documented pre-existing condition, the effect of a concomitant medication, a new condition which, based on the pathophysiology of the condition, and the pharmacology of the study drug, would be unlikely related to the use of the study drug.

Possible: The event follows a reasonable temporal sequence from administration of the study drug or the event follows a known response pattern to the study drug BUT the event could have been produced by an intercurrent medical condition which, based on the pathophysiology of the condition, and the pharmacology of the study drug, would be unlikely related to the use of the study drug or the event could be the effect of a concomitant medication

Probable: The event follows a reasonable temporal sequence from administration of the study drug and the event follows a known response pattern to the study drug AND the event cannot have been reasonably explained by an intercurrent medical condition or the event cannot be the effect of a concomitant medication

Definite: The event follows a reasonable temporal sequence from administration of the study drug, the event follows a known response pattern to the study drug and based on the known pharmacology of the study drug, the event is clearly related to the effect of the study drug

Unknown: Based on the evidence available, causality cannot be ascribed

### 8.3 Recording and Reporting

#### 8.3.1 Serious Adverse Events Reportable to the FDA

Investigators and other site personnel must inform the FDA, via a MedWatch form, of any serious or unexpected adverse events that occur in accordance with the reporting obligations of 21 CFR 312.32, and will concurrently forward all such reports to AZ. A copy of the MedWatch report must be faxed to AstraZeneca at the time the event is reported to the FDA. It is the responsibility of the investigator to compile all necessary information and ensure that the FDA receives a report according to the FDA reporting requirement timelines and to ensure that these reports are also submitted to AstraZeneca at the same time.

A cover page should accompany the MedWatch form indicating the following:

- ZD6474 Investigator Sponsored Study (ISS)
- The investigator IND number assigned by the FDA
- The investigator's name and address
- The trial name/title and AstraZeneca reference number

Investigative site must also indicate, either in the SAE report or the cover page, the causality of events in relation to all study medications and if the SAE is related to disease progression, as determined by the principal investigator.

***Send SAE report and accompanying cover page by way of fax to AstraZeneca's designated fax line: [contact], Attention ZACTIMA ISS Safety Representative***

To report to the local IRB, please follow SAE guidelines as outlined by the Office for the Dana Farber/Harvard Cancer Center Protection of Research Subjects (OPRS). Guidelines can be found on their website: .

If a non-serious AE becomes serious, this and other relevant follow-up information must also be provided to AstraZeneca, the FDA and Dana Farber / Harvard Cancer Center OPRS.

Serious adverse events that do not require expedited reporting to the FDA need to be reported to AstraZeneca preferably using the MedDRA coding language for serious adverse events. This information should be reported on a monthly basis and under no circumstance less frequently than quarterly.

**All SAEs have to be reported to AstraZeneca, whether or not considered causally related to the investigational product. All SAEs will be documented.**

### 8.3.2 Annual IND Report

In accordance with the regulation 21 CFR § 312.32, the Sponsor-Investigator shall within 60 days of the anniversary date that the IND went into effect submit a brief report of the progress of the investigation. Please refer to Code of Federal Regulations, 21 CFR § 312.32 for a list of the elements required for the annual report. All IND annual reports submitted to the FDA by the Sponsor-Investigator should be copied to Astra Zeneca.

### 8.3.3 Study Records

Study data will be collected in a standardized case report form (CRF). The investigator will record all patient information, including patient identification, tumor status, previous treatment, as well as information concerning drug administration, results of laboratory tests, toxicity and efficacy data.

## 9 STUDY CALENDAR

### 9.1 Pre-registration work-up

Informed consent must be obtained prior to performing any tests or procedures that are being done specific for the enrollment to this study. Medical history; clinical examination; ECOG PS; vital signs will be performed no sooner than 4 weeks prior to start of therapy; hematology; biochemistry; EKG will be performed within 7 days of initiation of protocol therapy. Appropriate radiographic procedures to document

extent of disease will be performed within 4 weeks prior to initiation of protocol therapy. Follow-up tumor assessments must be performed using the same method for a given patient (e.g. CT scan, Magnetic Resonance Imaging, X-rays, ultrasounds, scintigraphy, endoscopy). Ultrasound examination should only be used to detect new lesions or confirm subcutaneous skin lesion sizes. All concomitant medications will also be documented

## 9.2 Evaluation during treatment

Clinical examination including a complete physical examination, ECOG PS, vital signs, hematology, biochemistries, toxicity assessment and documentation of concomitant medications will be performed as noted in below required data table (Section 10). Toxicity will be assessed according to the NCI CTCAE V 3.0.

Initial tumor response will be assessed every 8 weeks and tumor assessment should be repeated no sooner than 4 weeks after a response for confirmation.

## 9.3 Post-treatment follow-up

After the end of study treatment (whatever the reason for discontinuation), the patient will be followed for at least one month, during which time all procedures for the reporting of SAEs will be followed. All patients who discontinue the trial secondary to an adverse event should be followed until resolution, stabilization or return to a baseline condition. Patients who discontinue the trial without documented tumor progression should be evaluated for extent of disease at the time of trial discontinuation.

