### 2.2 SECONDARY

Determine response rate, progression-free survival and overall survival of adding ZD6474 to cetuximab and irinotecan in patients with metastatic colorectal cancer previously treated.

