### 3.5 DURATION OF THERAPY

Patients will continue the study treatment until disease progression, unacceptable toxicity, or development of any of the criteria for patient discontinuation as described in Section 11 of the protocol.

Patients will be considered to be on-study for the duration of their treatment and during the 30 days following treatment discontinuation. Treatment discontinuation is defined as the last day of study treatment.

All included patients will be followed up until recovery or stabilization of all adverse events or return to baseline condition.

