## 12.1 Eligibility

Though the primary endpoint is determination of an MTD, the secondary endpoint of efficacy is very important in this study and patients must have measurable disease by RECIST.

**Measurable disease** - the presence of at least one measurable lesion. If the measurable disease is restricted to a solitary lesion, its neoplastic nature should be confirmed by cytology/histology.

**Measurable lesions** - lesions that can be accurately measured in at least one dimension with longest diameter  $\geq 20$  mm using conventional techniques or  $\geq 10$  mm with spiral CT scan.

**Non-measurable lesions** - all other lesions, including small lesions (longest diameter  $< 20$  mm with conventional techniques or  $< 10$  mm with spiral CT scan), i.e., bone lesions, leptomeningeal disease, ascites, pleural/pericardial effusion, inflammatory breast disease, lymphangitis cutis/pulmonis, cystic lesions, and also abdominal masses that are not confirmed and followed by imaging techniques.

All measurements should be taken and recorded in metric notation, using a ruler or calipers. All baseline evaluations should be performed as closely as possible to the beginning of treatment and never more than 4 weeks before the beginning of the treatment.

The same method of assessment and the same technique should be used to characterize each identified and reported lesion at baseline and during follow-up. Clinical lesions will only be considered measurable when they are superficial (e.g., skin nodules and palpable lymph nodes). For the case of skin lesions, documentation by color photography, including a ruler to estimate the size of the lesion, is recommended.

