## 12.5 Evaluation of best overall response

The best overall response is the best response recorded from the start of the treatment until disease progression/recurrence (taking as reference for PD the smallest measurements recorded since the treatment started). In general, the patient's best response assignment will depend on the achievement of both measurement and confirmation criteria

| Target lesions | Non-Target lesions | Evaluation of non-target lesions | Overall response |
|-----------------------|---------------------------|-----------------------------------------|-------------------------|
| CR                    | CR                        | No                                      | CR                      |
| CR                    | Incomplete response/SD    | No                                      | PR                      |
| PR                    | Non-PD                    | No                                      | PR                      |
| SD                    | Non-PD                    | No                                      | SD                      |
| PD                    | Any                       | Yes or No                               | PD                      |
| Any                   | PD                        | Yes or No                               | PD                      |
| Any                   | Any                       | Yes                                     | PD                      |

Patients with a global deterioration of health status requiring discontinuation of treatment without objective evidence of disease progression at that time should be classified as having "symptomatic deterioration". Every effort should be made to document the objective progression even after discontinuation of treatment.

In some circumstances it may be difficult to distinguish residual disease from normal tissue. When the evaluation of complete response depends on this determination, it is recommended that the residual lesion be investigated (fine needle aspirate/biopsy) to confirm the complete response status.

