### 13 Statistical Considerations

This is a phase I study, initially with dose escalation of ZD6474 and then adding irinotecan. The study will likely accrue between 6 and 15 patients (before MTD testing) with the described dose escalation schema, though it could range from 3 to 34 patients. We expect accrual to be 2-3 patients / month (though this will vary during waiting periods to proceed to next dose level). If patients in dose levels 2-4 who have a DLT in the first 14 days (prior to initiation of irinotecan), the patient will not be counted towards the DLTs of that cohort and an additional patient will be substituted. For example, if one of the first 3 patients in dose level 4 have a DLT, that patient will not be calculated into the DLT tabulation for ZD6474,

cetuximab and irinotecan and an additional patient will be substitute in that spot. If this scenario occurs twice, the study will be held and the study team will reevaluate the ZD6474 / cetuximab toxicity profile. To ensure the toxicity at the MTD is acceptable and to further define any toxicity that may occur with this regimen, an additional 10 patients will be accrued at the MTD. The estimation of toxicity rate will be based on these 10 additional patients. With 10 patients, the 90% confidence bounds for any toxicity will be  $\pm 28\%$ . The probability of a dose level declared too toxic based on the true DLT rate is defined as such:

| True DLT Rate | Probability of declaring dose too toxic |
|---------------|-----------------------------------------|
| 20%           | 0.29                                    |
| 30%           | 0.51                                    |
| 40%           | 0.69                                    |
| 50%           | 0.83                                    |
| 60%           | 0.92                                    |

Response rate, progression-free survival and overall survival are secondary analyses. Each will be reported by dose level and at the MTD.

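### Overall and progression-free survival are secondary endpoints, but the Protocol requires no vital-status follow-up beyond a minimum one-month safety period and schedules no imaging after the evaluation at discontinuation

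*Protocol*

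**What the plan says.** **What is promised.** The secondary objective in Section 2.2, repeated in the synopsis, is to "Determine response rate, progression-free survival and overall survival of adding ZD6474 to cetuximab and irinotecan". Section 13 states that "Response rate, progression-free survival and overall survival are secondary analyses" and commits to reporting each by dose level and at the MTD.

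**What is collected after treatment.**
- Section 3.5 ends treatment at progression, unacceptable toxicity or another discontinuation criterion. It sets the on-study period: "Patients will be considered to be on-study for the duration of their treatment and during the 30 days following treatment discontinuation".
- Section 9.3 sets the follow-up: "the patient will be followed for at least one month, during which time all procedures for the reporting of SAEs will be followed".
- Follow-up beyond that has an adverse-event purpose. Section 3.5 says "All included patients will be followed up until recovery or stabilization of all adverse events or return to baseline condition", and Sections 9.3 and 11 say much the same for patients who stop because of an adverse event. None of these runs to death.
- The Section 10 table has no entry after study withdrawal, for survival contact or for imaging.

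**Tumour assessment off treatment.** The 8-weekly assessment stands in Section 9.2, which covers evaluation during treatment. For those who leave without progression, Section 9.3 says "Patients who discontinue the trial without documented tumor progression should be evaluated for extent of disease at the time of trial discontinuation". Section 12.5, on symptomatic deterioration, adds "Every effort should be made to document the objective progression even after discontinuation of treatment" but gives no schedule.

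The Protocol defines neither OS nor PFS and gives no censoring rule for either.

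**The concern.** An OS analysis needs a date of death or a last-known-alive date for each patient, over a period long enough for deaths to occur. Treatment stops at progression, so a patient alive at progression enters a window of about one month, after which the Protocol asks for no further information on survival.

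Two consequences follow if the required minimum is what happens in practice. Few deaths are recorded. And those who drop out of the risk set are mostly patients who have just progressed, whose risk of death is higher than that of patients still on treatment. Kaplan-Meier estimation treats the two groups as exchangeable, so the curve would sit too high.

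PFS has a smaller version of the problem. Under Section 7.1 a patient whose toxicity has not resolved to grade 1 within 3 weeks is withdrawn. Such a patient has one disease evaluation at discontinuation and no scheduled scan afterwards, so the date of a later progression may never be known.

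This is a question of which data are collected. An analysis plan can define endpoints and censoring, but it cannot supply death dates or scans that were not obtained.

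**Working it through.** **The Protocol's own figure.** There is none to reproduce: it states no OS or PFS median, event count, power or precision.

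**Inputs from the Protocol.** Follow-up of 30 days after the last dose (Section 3.5), or 30/30.4375 = 0.986 months. At most 34 patients (Section 3.3), of whom 10 are added at the MTD (Section 13).

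**Assumed inputs.** The Protocol gives none of the following.
- m: median survival after treatment ends, exponential, 3 to 12 months.
- q: share of patients whose treatment ends in death, 5 to 10%.
- Follow-up stops at the 30-day minimum, and every patient eventually dies (Section 1.1 calls metastatic disease incurable).

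**Step 1: share of deaths observed.**

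Share of post-treatment deaths seen = 1 − 2^(−0.986/m).

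Share of all deaths seen = q + (1 − q) × [1 − 2^(−0.986/m)].

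For m = 6: 1 − 2^(−0.986/6) = 0.1076. With q = 0.05 the total is 0.05 + 0.95 × 0.1076 = 0.152. With q = 0.10 it is 0.10 + 0.90 × 0.1076 = 0.197.

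| m (months) | Post-treatment deaths seen | All deaths seen, q = 5% | All deaths seen, q = 10% | Deaths seen among 34 | Deaths seen among 10 |
|---|---|---|---|---|---|
| 3 | 20.4% | 24.3% | 28.3% | 8.3 to 9.6 | 2.4 to 2.8 |
| 6 | 10.8% | 15.2% | 19.7% | 5.2 to 6.7 | 1.5 to 2.0 |
| 12 | 5.5% | 10.3% | 15.0% | 3.5 to 5.1 | 1.0 to 1.5 |

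The conclusion is not sensitive to these choices. At m = 2 the share seen is 33 to 36%. With q raised to 20% it is 24% (m = 12) to 43% (m = 2). Fewer than half of deaths are seen throughout.

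**Step 2: effect on the Kaplan-Meier median.** Simulation with 400,000 patients per scenario, exponential treatment duration, independent exponential survival after treatment, and censoring 30 days after treatment ends. Treatment medians of 2, 4 and 8 months are assumed.

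| Median treatment | m | q | True median OS | Kaplan-Meier median |
|---|---|---|---|---|
| 4 | 6 | 5% | 11.5 | 29.1 |
| 4 | 6 | 10% | 11.1 | 22.6 |
| 2 | 12 | 10% | 13.3 | 17.2 |
| 8 | 12 | 5% | 23.1 | 81.2 |

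All values are in months. The last two rows are the smallest and largest relative overstatements among the 18 scenarios run (17.2/13.3 = 1.3 and 81.2/23.1 = 3.5). The Kaplan-Meier median exceeded the true one in all 18.

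**Step 3: what longer follow-up recovers.** Share of post-treatment deaths captured, 1 − 2^(−f/m), for follow-up of f months:

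| f | m = 3 | m = 6 | m = 12 |
|---|---|---|---|
| 30 days | 20% | 11% | 5.5% |
| 6 | 75% | 50% | 29% |
| 12 | 94% | 75% | 50% |
| 24 | 99.6% | 94% | 75% |

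**The case against.** The strongest reply is that one month is a floor. Section 9.3 sets a minimum, and Section 3.5 only defines when a patient counts as on study; neither forbids collecting death dates later. The front sheet ticks medical record review, which is a route to those dates. The Section 10 table also has no column for the one-month follow-up that Section 9.3 does require, so a missing column does not prove that follow-up is not done. A reader might infer from Sections 3.5 and 9.3 that patients are followed for 30 days only and that OS cannot be estimated. The documents do not support that as a fact; it holds only if sites stop at the minimum. What remains is that longer follow-up is neither required nor scheduled, and is left to each of three centres.

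A reader might also infer that PFS is censored at withdrawal for toxicity. The Protocol contains no such rule, and a rule of that kind is commonly left to an analysis plan. Section 12.5 points the other way by asking for progression to be documented after treatment stops, although it is written for symptomatic deterioration and sets no schedule.

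Section 12.1 says that "the secondary endpoint of efficacy is very important in this study". That sentence explains why measurable disease is required for entry, and it should not be read as giving weight to OS.

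Finally, this is a phase I trial of 3 to 34 patients with an MTD objective. OS and PFS carry no hypothesis or precision target. This is correct and limits the severity, but it does not remove the mismatch between a listed endpoint and the data required for it.

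**Conclusion.** The point holds in a conditional form. The Protocol commits to reporting OS and PFS but requires no vital-status follow-up past a minimum one-month safety period and no imaging after the evaluation at discontinuation. If sites do only what is required, about 10 to 28% of deaths would be observed: roughly 3.5 to 10 among 34 patients and 1 to 3 among the 10 added at the MTD. The Kaplan-Meier estimate of OS would be biased upward because censoring falls at the end of treatment, mostly at progression.

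The percentages rest on assumed exponential survival, medians of 3 to 12 months and 5 to 10% on-treatment deaths. The direction does not depend on the exact values. The simulated medians illustrate the bias and do not predict this trial's results.

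For PFS the conclusion is only that patients withdrawn for toxicity without progression may lack later progression data. Dose escalation, DLT assessment and the MTD are unaffected. Severity is minor to moderate.

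**What to change.** In Sections 3.5, 9.3 and 10, add vital-status follow-up by phone or chart review, for example every 3 months, until death or a fixed cut-off date. State that it is separate from the 30-day safety period. The cut-off should be set with Step 3 in mind: at m = 6 months, 12 months of follow-up captures 75% of post-treatment deaths and 24 months captures 94%.

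For patients who stop without progression, record the progression date from scans done in routine care until progression or new anticancer therapy. Mandated extra scans would cost more and are not needed for this point.

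If the sponsor does not want survival follow-up, remove OS from the synopsis, Section 2.2 and Section 13.

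The cost is an amendment and a modest amount of phone or chart work for at most 34 patients. No new study procedure is needed, and medical record review is already marked on the front sheet.
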